## Abstract

**Background:**

Causes and consequences of chronic stress levels in the context of healthcare work are well examined. Nevertheless, the implementation and evaluation of high-quality interventions to reduce stress of healthcare workers is still missing. Internet and app-based interventions are a promising venue for providing interventions for stress reduction to a population that is otherwise difficult to reach due to shift work and time constraints in general. To do so, we developed the internet and app-based intervention (fitcor), a digital coaching of individual stress coping for health care workers.

**Methods:**

We applied the SPIRIT (Standard Protocol Items: Recommendations for Interventional Trials) statement as a guideline for the present protocol. A randomized controlled trial will be conducted. There are five different intervention groups and one waiting control group. To achieve the sample sizes required by power analysis (G*Power) (β-error 80%; effect size 0.25), the sample sizes of the respective scenarios will be at best as follows: 336 care workers from hospitals, 192 administrative health personnel, 145 care workers from stationary elderly care homes, and 145 care workers from ambulatory care providers in Germany. Participants will randomly be assigned to one of five different intervention groups. A crossover design with a waiting control group is planned. Interventions will be accompanied by three measurement points, first a baseline measure, second a post-intervention measure directly after completion of the intervention, and a follow-up measure 6 weeks after completion of the intervention. At all three measurement points, perceived team conflict, work-related experience patterns, personality, satisfaction with internet-based training, and back pain will be assessed using questionnaires, as well as heart rate variability, sleep quality, and daily movement will be recorded using an advanced sensor.

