The proposed trial is needed to address these aims for four reasons. It includes samples from three different health care settings (1), namely hospitals, stationary elderly care homes, and ambulatory care, which allows to draw conclusions on similarities and differences between the effectiveness of the interventions in the specific settings. It allows comparison of different digital interventions with regard to topic, complexity, or biofeedback inclusion (2). Additionally, it enables investigating stress both from an objective perspective facilitating physiological measures as well as from a subjective perspective facilitating self-report measures (3). Finally, we can derive conclusions on long-term effects of the applied intervention through our longitudinal approach [4]. We expect that each intervention will benefit participants as they get free access to usually pricey digital health improvement programs. But at the same time, participants will have to invest some of their time to conduct all three measurement time points. Other than that, no harms are assumed to appear directly caused by the intervention. Next to the effects on different outcome parameters, the whole approach will give us more information about the required composition of individualization and modularization in different occupational groups.

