### Participants

#### Eligibility and ethical approval

The crossover randomized controlled trial will include nursing staff and office workers aged 18 years or older from hospitals, stationary elderly care facilities, and ambulatory care providers. No clinical patients will be involved in the proposed study. Fluency in the German language as well as internet access via a smartphone device are prerequisites for study participation. All potential participants will be informed about the study and its procedure through a comprehensive informative video. The study is conducted in agreement with the principles of the Declaration of Helsinki and the guidelines of Good Clinical Practice. The recruitment of the participating nursing facilities involved cooperating health insurance companies, whereas the recruitment within the participating facilities will remain within the responsibility of the authors. Written informed consent will be obtained from all participants or their legal guardians before enrolment. Participants as well as their relatives or legal guardians can withdraw consent at any time. The local ethics committee of the TU Berlin, Germany, has approved the study protocol (No GR_14_20191217). The trial was registered at DRKS.de with registration number DRKS00021423 on 12 July 2021.

We used the program G*Power [81] to calculate the relevant sample size. To achieve the sample sizes required by power analysis with a β-error of 80% and an effect size of 0.25, we will need to include 700 participants. An effect size of 0.25 is considered a small effect, which is congruent with the literature on the effectiveness of eHealth/mHealth behavior change interventions [82, 83] and workplace health promotion interventions [84]. We expect a participation rate of 20% as this appeared to be a realistic participation rate in previous intervention studies in different small and middle-sized companies [85]. With an expected dropout rate of 20%, we will include additional 140 participants to ensure that the study results will still be eligible for data analyses.

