#### Statistical analysis

Primary and secondary outcomes will be analyzed using SPSS software. The study will allow a comparison between all summarized intervention groups with the waiting control group, as well as a comparison between the different intervention groups. Additionally, participation rates will be included in the analyses. Sample characteristics will be explored applying descriptive statistics. Standard analyses adjustments will be made to adjust for baseline differences between groups, in case there are any. For missing data, sensitivity analyses will be conducted to compare results with the complete case analysis. Further, different options for imputation will be considered. Differences between intervention groups and the control group will be investigated using *χ*
^2^ tests for categorical variables and independent sample *t*-tests for continuous variables. General linear mixed models will be applied for the statistical analyses of primary and secondary outcomes. Group-based trajectory modelling will also be applied if feasible given the data situation. The models will be adjusted by baseline value and potential confounders, such as staff field of working (hospital, stationary elderly care, ambulatory care) or age. *P* values <.05 will be considered as statistically significant and effect sizes of >.3 will be regarded as clinically significant. If appropriate, 95% CI will be reported with the *p* values as well. If feasible, missing data will be imputed through multiple imputation.

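### The abstract ties the four setting sizes (336, 192, 145, 145) to an 80% power analysis, but they match neither stated total, and 80% within the 145 and 192 settings is not secured for the T2 comparison with an untreated control

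*Protocol article*

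**What the plan says.** Abstract, Methods: the sentence opens "To achieve the sample sizes required by power analysis (G*Power) (β-error 80%; effect size 0.25". After that clause it goes on to say that "the sample sizes of the respective scenarios will be at best as follows: 336 care workers from hospitals, 192 administrative health personnel, 145 care workers" in elderly care homes, with a further 145 in ambulatory care. The list is qualified by the words at best.

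Eligibility and ethical approval: the same G*Power inputs lead to one total, "we will need to include 700 participants". A further 140 are added for an expected 20% dropout, which makes 840. The paragraph also says "An effect size of 0.25 is considered a small effect". It names neither the metric nor the test.

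Introduction, end of the section on digital interventions: the first of four reasons for the trial is that sampling from hospitals, elderly care homes and ambulatory care "allows to draw conclusions on similarities and differences between the effectiveness of the interventions in the specific settings".

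Statistical analysis: the contrasts foreseen are a "comparison between all summarized intervention groups with the waiting control group, as well as a comparison between the different intervention groups". Mixed models are adjusted for baseline value and for potential confounders, with field of working as an example.

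Study design and Data collection: measurements are at T1, T2 (8 weeks) and T3 (16 weeks). The waiting group receives an intervention between T2 and T3.

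**The concern.** The abstract speaks of required sample sizes in the plural and then gives one size per setting. The natural reading is that each size delivers 80% power. Each setting is, however, divided over five interventions and a waiting control, so a setting of 145 has about 24 people per group, or about 19 after 20% dropout.

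A reader who trusts the 80% would take a null result in elderly care or ambulatory care as coming from an adequately powered comparison, and would take an apparent difference between settings as informative. Setting-specific effectiveness is the first reason given for the trial, so the power behind it should be stated correctly.

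**Working it through.** **Inputs.** From the protocol: sizes 336, 192, 145 and 145; power 80% (printed as a β-error of 80%); effect size 0.25; alpha 0.05; dropout 20%; five interventions plus waiting control. Assumed, because the protocol does not say: two-sided tests, an equal six-way split, the metric (both Cohen's f = 0.25 and a standardised mean difference d = 0.25 were tried), and the correlation r between baseline and T2.

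**Totals.** 336 + 192 + 145 + 145 = 818, against 700 and 700 + 140 = 840. Taking 20% dropout off 818 leaves 654, below 700.

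**Reproducing the plan's sizes.** The closest standard routine is the repeated-measures ANOVA for between factors, with λ = f²·N·m / (1 + (m − 1)ρ). With f = 0.25, six groups, m = 3 and ρ = 0.5 (assumed), 80% needs N = 143, or 144 in equal groups. At 145, λ = 0.0625 × 145 × 3 / 2 = 13.6 and power is 80.8%. After dropout (N = 116) it is 69.5%. With 12 groups the routine needs 190, or 192 in equal groups, but the protocol describes no 12-group test. No variant tried gave 336, and none gave all four sizes. This routine averages T1, T2 and T3. T1 precedes treatment, and by T3 the waiting group has been treated, so it does not test the contrast with an untreated control.

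**Six-group F test at T2, f = 0.25.** Unadjusted, λ = f²·N with 5 and N − 6 degrees of freedom: 0.0625 × 145 = 9.06 and 0.0625 × 192 = 12.0. With baseline adjustment, λ is divided by 1 − r², and one further degree of freedom is lost.

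| N | Unadjusted | r = 0.5 | r = 0.6 | 80% reached from r of about |
|---|---|---|---|---|
| 145 | 61% | 75% | 83% | 0.57 |
| 116 (145 less 20%) | 49% | 63% | 72% | 0.69 |
| 192 | 75% | 88% | 93% | 0.31 |
| 154 (192 less 20%) | 64% | 78% | 85% | 0.53 |
| 336 | 96% | 99% | >99% | 0 |

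Unadjusted, 80% needs 211 per setting (216 in equal groups). The allocation section describes sets of five. With five groups, unadjusted power is 65% at 145 and 79% at 192.

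**Two-group contrasts at T2, unadjusted.** The noncentrality of the t test is d·√(n₁n₂/(n₁ + n₂)). For one arm against control, n₁ = n₂ = N/6. At N = 192 and d = 0.5 this is 0.5 × √(32 × 32/64) = 2.0. For all interventions against control, n₁ = 5N/6 and n₂ = N/6. At N = 336 and d = 0.25 this is 0.25 × √(280 × 56/336) = 1.71.

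| N | One arm vs control, d = 0.5 | One arm vs control, d = 0.25 | Pooled vs control, d = 0.5 | Pooled vs control, d = 0.25 |
|---|---|---|---|---|
| 145 | 40% | 14% | 61% | 20% |
| 192 | 50% | 17% | 73% | 25% |
| 336 | 75% | 26% | 93% | 40% |

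With baseline adjustment at r = 0.7 and d = 0.5, one arm against control reaches 66% at 145 and 79% at 192.

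**Whole trial, N = 700, d = 0.25, unadjusted.** Pooled interventions against control: 69%. Arm against arm: 48%. At f = 0.25 the six-group F test exceeds 99%.

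**The case against.** The strongest reply is that no passage promises 80% power in each setting. The eligibility section gives one overall requirement, the abstract says at best, and 818 lies near 840, so the four sizes may be a recruitment breakdown. The analysis section uses field of working as an adjustment variable and plans no test within a setting. This stands in part: per-setting power is a strong reading of the abstract, not an explicit guarantee. But the abstract is worded so that readers will take it that way, and the Introduction relies on setting-specific conclusions.

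A reader might infer that the smaller settings simply fail to reach 80%. The documents do not support that. Baseline adjustment is planned, and under it 192 passes 80% at a modest correlation and 145 at a moderate one. Nor is 145 a plain arithmetic slip, since a standard routine yields it almost exactly. The full protocol, which is not shown, may name the test.

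The intervention arms can also be compared with each other at T3, so the restriction to T2 applies only to contrasts with the waiting group. That is correct, and the point is limited accordingly.

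Finally, a reader might infer that the trouble is confined to the small settings, or that the 80% is safe for the pooled sample. Neither follows. If 0.25 is a standardised mean difference, 336 falls short as well, and so do the contrasts at N = 700 shown above.

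**Conclusion.** The point holds as a mismatch between two sample-size statements and as a power claim that is not secured within settings. That the four sizes match neither stated total needs no assumption. The shortfall in the six-group test at 145 and 192 rests on f = 0.25, an equal six-way split and two-sided 5% tests; it is clear without adjustment and depends on the unstated baseline correlation with it. Dropout raises the correlation needed to about 0.69 and 0.53. The shortfall for single arms against control is firmer: in these two settings no case examined reaches 80% at d = 0.25 or d = 0.5, even at r = 0.7. The change should be made, but it concerns what is claimed from the sample and does not show that the trial is the wrong size.

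**What to change.** - Reconcile the abstract with the eligibility section (818 against 700 and 840), and say whether the setting sizes include the dropout allowance.
- Call 336, 192, 145 and 145 recruitment targets per setting, and stop attributing 80% power to each.
- State which test, effect-size metric and sample the 80% refers to. Recompute it for the pooled sample first; do not assume that it holds there.
- In the Introduction, present setting-specific effectiveness as exploratory. Estimate it from the planned pooled, baseline-adjusted model with an added setting-by-group term, and report estimates with 95% confidence intervals.
- If any within-setting power is printed, give its assumptions: metric, baseline correlation and number of groups.

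The cost is rewording in three places, one recalculation and one model term. No extra participants are needed. The downside is a less favourable stated power for the setting-specific results.

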**Discussion:**

Workers in the health care sector increasingly face high job demands and stress levels. Traditional health interventions fail to reach the respective population due to organizational constraints. Implementation of digital health interventions has been found to improve stress coping behavior; however, the evidence in health care settings has not been established. To the best of our knowledge, fitcor is the first internet and app-based intervention to reduce stress among nursing and administrative health care personnel.

**Trial registration:**

The trial was registered at DRKS.de on 12 July 2021, registration number: DRKS00024605.

## Introduction

### Background and rationale

Occupational psychosocial stress can increase the risk to develop psychological, musculoskeletal, or cardiovascular disease [1, 2]. Especially health personnel around the globe experience exceptionally high levels of occupational stress [3] leading to serious individual, organizational, and societal problems [4]. Additionally, healthcare institutions in various European countries indicate staff shortages, and often fail to retain long-term personnel, exposing health personnel to a vicious cycle of stress and extra work [5]. This is in line with findings in Germany that report job demands in the health sector to be considerably higher compared to other professions [6]. Similarly, within the European Union, it is well known that more than one in four nurses are overburdened [7]. Recurring stressors in health organizations include high work demands, leadership style, few participation opportunities for work structuring, emotional burdens, lack of appreciation, and work-family conflicts [8, 9]. In turn, these stressors may influence recreational activities of affected persons. For instance, sleep and physical activity have been found to be poor in stressed individuals [10, 11]. Additionally, individuals with lower heart rate variability (HRV) were more likely to report poorer sleep quality in the context of chronic stressor exposure than individuals with higher HRV [12]. Frequent or chronic occupational stress is linked to serious health consequences. If work-related demands outweigh individual, social, and organizational resources [13], affected persons may incur psychological and physiological consequences such as sleep disorders, gastrointestinal complaints, burnout, diabetes, and coronary heart disease [14–17]. In severe cases, inability to work can lead to long-term sickness absenteeism [18].

In general, psychosocial stressful stimuli activate neuronal, neuroendocrine, and endocrine pathways. A physiological response to stress occurs thus, among others, at the neurological level, through receptors of the sympathetic nervous system that stimulate the sympatico-adrenomedullary axis. The hormones adrenaline and noradrenaline are released in the adrenocortical medulla, leading to an increase in heart rate and a decrease in heart rate variability (HRV) under physical or psychological stress [19]. Such biological responses to stressful stimuli may be adaptative. However, extreme, frequent, or chronic activations of stress axes may be detrimental to health and may be assessable via heart rate variability [20, 21]. Chronically low HRV is associated with impaired regulatory and homeostatic functions of the autonomic nervous system, which reduce the body’s ability to cope with internal and external stressors. Thus, HRV measurement is a noninvasive method that can be used to measure the autonomic nervous system in a variety of settings [22]. Studies show that for example in response to stress-inducing tasks, such as the Trier Social Stress Test, test participants show low parasympathetic activity, characterized by a decrease in High-Frequency Power (HF) and an increase in Low-Frequency Power (LF) HRV values [23–25]. The Standard Deviation of Normal-to-Normal heart beats (SDNN value) represents an index of physiological resilience to stress. When HRV is elevated and irregular, SDNN increases. On the other hand, especially when chronically stressed (e.g., at work), the SDNN value decreases [22, 26]. A low Root Mean Square of Successive Differences (RMSSD) value can also be an indicator of stress. Here, again, studies show that especially in chronic stress, values are lower than in non-stressed individuals [19, 25, 27]. However, it should be noted when evaluating HRV data that—beyond psychological stress—certain influencing variables must be considered. Age has a major influence on HRV. It increases initially, is highest in young adults, and decreases with increasing age [28, 29]. In addition, BMI correlates positively with sympathetic activity [30] and thus negatively with HRV [31, 32], whereas regular physical activity is associated with an increase in HRV [33, 34].

### Interventions to reduce stress

While health complaints are frequently observed, there are personal and organizational resources which can improve resilience towards occupational stress [35–37]. Personal resources with stress-protecting qualities include social support, coping style, self-efficacy, and optimism [38–41]. Pertaining to organizational resources, a recent systematic review identified supervisor support, job autonomy, and provision of work equipment to minimize stress [42].

Stress may differentially affect professions within the health sector [43]. For instance, nurses exhibit less health behaviors (e.g., physical activity) than physicians, pharmacists, and administrative health personnel [44]. According to Gerber & Pühse [45], physical activity may exert a stress-buffering effect and thus protect against physical and psychological illness. Also, within the nursing workforce, stressors vary between settings. For example, stressors in an outpatient care include long driving times and high emotional involvement with patients while this is less problematic in hospital settings [46].

Although a variety of stressors exist in the healthcare setting, evidence suggests that perceived stress can be reduced through participation in stress management interventions. For instance, mindfulness programs improve quality of life, anxiety, stress perception, and sleep quality [47, 48]. Physical activity-based studies showed improvements in autonomous nervous system function [49], accelerometric factors such as steps per day [50], BMI, sedentary behavior, MET, and physical activity levels [51]. More recently, mHealth interventions yield the potential to address stress in a low-cost, easy-to-implement fashion [52] with existing evidence for stress-reducing effects in different occupational settings [53].

Within the health care sector, efficacious stress reduction programs include Yoga and qigong [54], cognitive-behavioral interventions such as resilience training [55], mindfulness-based stress reduction (MBSR) [56], or multimodal combinations of aforementioned intervention types [57].

Despite the plethora of studies confirming the efficacy of stress reduction interventions, the evidence for health personnel is generally weak. Study rigor issues, for instance low total intervention time, small sample sizes, and failure to assess behavioral change undermine intervention quality [58]. Further, high risk of bias due to lack of both appropriate study designs and follow-up measurement points are common [54, 59].

The poor evidence base in the field of study is due to organizational, social, and individual reasons. According to Zhang et al. [60], participation in health promotion campaigns in health care facilities is often aggravated by various barriers. Specifically, amiss communication between management and staff, colleague peer pressure, insufficient staffing, top-down decision-making, and budget constraints can impede participation rates. Additionally, healthcare personnel are difficult to reach due to low motivation to change, low self-efficacy, and high psychological and physiological demands [61].

Moreover, due to differences in individual and organizational resources, stress management interventions should be tailored to the specific needs of participants. One possibility is to categorize subjects in terms of coping style when facing difficult work situations [60]. Further, there are individual preferences that need to be considered. For instance, health and other nonhealth-related outcomes (e.g., the value of a healthy future self and time costs, respectively) have differential impacts on the decision to engage in stress management [61]. Thus, one-size-fits-all interventions [62] should not be adapted for vulnerable populations as intervention success is limited [63].

In sum, to counteract stress effects in health personnel, low-cost, easy-to-implement, setting-specific, and need-tailored health promotion interventions are necessary. One way to address these issues is digital (mHealth) interventions.

